### Study design

This study is designed as a multi-center, prospective, observational, open cohort study. Initiation of recruitment has been staggered across sites, with the earliest commencing in February 2019 and additional sites beginning recruitment in 2021. Enrollment is scheduled to complete in December 2022, with follow-up to complete in June 2023. In total, approximately 2476 patients are expected to be enrolled in the study. Patients will be followed to collect key clinical and treatment-related data including overall survival and QOL metrics until death or loss to follow up. QOL metrics will be assessed at the time of study enrollment, prior to the initiation of treatment, and during post-treatment follow up (1 month after initiation of treatment, 3 months after initiation of treatment, and then every 3 months until death or loss to follow up). The accrual period is expected to range between 22 and 47 months across sites. Duration of follow up will differ by site due to the staggered initiation of recruitment, however, study participants will be followed for at least 6 months and up to a total of 53 months.

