#### Secondary endpoints

Secondary endpoints that will be assessed include health-related QOL, as measured by the ‘Modified Roseblatt Index,’ [16] major complications and treatment-related mortality. The ‘Modified Rosenblatt Index’ is a questionnaire assessing patient-reported outcomes previously developed for use among EC patients by Rosenblatt, et al., which has been adapted for use within a resource-limited context (see Table 2) [16]. Parameters evaluated as part of this index are scored on a Likert scale assessing the presence and severity of the following: Dysphagia, Odynophagia, ‘Chest and/or Back pain,’ World Health Organization (WHO) performance status, and ‘Overall Well-being’ since starting treatment. Secondary outcome measures related to dysphagia will also be assessed as dysphagia is commonly a dominant symptom among patients with advanced disease. These secondary measurements include time to achieve any dysphagia relief, time to achieve maximal dysphagia relief, duration of dysphagia relief, and dysphagia-adjusted survival.

**Table 2 Tab2:** Quality of life metrics as measured by ‘Modified Rosenblatt Index’^a^

	Score				
	0	1	2	3	4
**Dysphagia** Which of the following best describes your ability to swallow?	Normal	Can swallow most foods	Can swallow a soft diet	Can swallow fluids only	Unable to swallow saliva
**Odynophagia** Which of the following best describes the severity of pain you experience when swallowing?	No pain	Mild pain	Moderate pain	Severe pain	–
**Regurgitation** Which of the following best describes how frequently you experience acid reflux, heart burn and/or the sensation of burning in the esophagus?	Never	Infrequent	Frequent	Constant	–
**Chest-back pain** Which of the following best describes your chest and/or back pain?	No pain	Pain relieved by non-narcotics	Pain not relieved by non-narcotics or requiring an opiate medication	–	–
**WHO Performance status** Which of the following best describes your symptoms and activity level on a daily basis?	Fully active, able to carry on all pre-disease performance without restriction	Restricted in physically strenuous activity but ambulatory and able to carry out work of a light or sedentary nature	Ambulatory and capable of all selfcare but unable to carry out any work activities. Up and about more than 50% of waking hours	Capable of only limited selfcare, confined to bed or chair > 50% of waking hours	Completely disabled. Cannot carry on any selfcare. Totally confined to bed or chair

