#### Chart abstraction

Clinical information will be abstracted from the patient’s medical record at baseline (at time of study enrollment), during treatment(s), and following completion of any treatment(s). Clinical and treatment data collected through chart abstraction is summarized in Table 3. Treatment data will include dates of treatment, procedural details (stenting, esophagectomy, gastrostomy tube placement), radiation treatment regimens, chemotherapy regimens, major treatment- and disease-related complications, best response to treatment (if evaluated), reasons for discontinuing treatment or pursuing supportive care, and date and cause of death. Data will be collected on the time elapsed from diagnosis to initiation of treatment to account for any treatment delays that may explain differences in survival during analyses.

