Cochran-Armitage test will be used to compare symptom metrics assessed using the ‘Modified Rosenblatt Index’ (Dysphagia, Odynophagia, ‘Chest and/or Back pain,’ WHO performance status, and ‘Overall Well-being’ since starting treatment) between each of the different palliative EC treatments (chemotherapy, radiotherapy, chemoradiation, esophageal stenting, basic supportive care) at each time point: 1 month after initiation of treatment, 3 months after the initiation of treatment and then every 3 months thereafter. We will also test for within-subject differences in scores between baseline (or pre-treatment) and each of post-treatment time points by McNemar’s Chi-squared test. In addition, generalized estimating equations (GEE) framework will be applied to analyze this longitudinal QOL data, where the treatment will be considered as the fixed effect and the subject-specific effects are the random effects.

Complications will be summarized as number of patients (%) with 95% confidence intervals and compared between treatment arms by Chi-squared test. Among palliative interventions, secondary outcome measures related to dysphagia will be compared using log-rank test and cph models to adjust covariates, including age, sex and baseline clinical covariates. ‘Time to achieve any dysphagia relief’ will be defined as time from treatment to improvement in dysphagia score of greater than or equal to 1. ‘Duration of dysphagia relief’ will be defined as time elapsed after treatment with any improvement in dysphagia from baseline. ‘Dysphagia-adjusted survival’ will be defined as the total time period with a dysphagia score of 0 to 2.

Measures of healthcare utilization and process measures related to the delivery of ESCC treatment by treatment approach will be examined as exploratory endpoints. Time-to-event measures will be compared among treatment groups by log-rank test. Count of hospitalization events, and total number of days hospitalized during and after ESCC treatment will be compared among treatment groups by ANOVA (or Kruskal Wallis test when normality assumption is not held). Chi-squared test will be used to compare the need for subsequent intervention for recurrent or persistent dysphagia by treatment approach. All analyses will be performed overall and within each site.

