Palliative interventions for EC have been an active area of research over the last several decades. Most of this research has taken place in HICs, with several RCTs having investigated best practices for palliation among patients with either ESCC or esophageal adenocarcinoma [9]. These studies highlight the tradeoffs between esophageal stenting with SEMS and the use of radiation-based therapies in patients with advanced disease [22, 23]. SEMS have been shown to provide immediate dysphagia relief, but are prone to failure over time due to stent migration and/or recurrent obstruction. Radiation-based therapies, including external beam therapy (EBRT) with or without chemotherapy and brachytherapy, have delayed effects, but may offer more durable symptom control. Steyerberg et al. developed and validated a prognostic index to help guide treatment selection in this patient population, with the rationale that SEMS may be advantageous for those with short life expectancies [24]. Subsequent efforts to evaluate this index in a South African patient population found that it had poor predictive value in this context, highlighting the challenges of generalizing evidence from clinical trials in HICs to low resource settings [25]. Advanced dysphagia, severe weight loss, and malnutrition are all much more prevalent among patients with EC in these settings. Access to supportive care is often more limited as well. These differences, both in terms of patient characteristics and health system factors, underscore the importance of advancing research on treatment strategies for ESCC in sub-Saharan Africa, with the goal of optimizing treatment delivery in this context. Although RCTs remain the gold standard in comparative effectiveness research, several challenges emerge with this study design in Eastern Africa, including the ethics of randomizing patients who are often in poor general condition, and the time, infrastructure and resources needed for implementing well-designed clinical trials [26, 27].

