The TOEC-Eastern Africa study is timely as efforts are currently underway to improve access to oncologic care throughout Eastern Africa as well as other regions in Africa. Historically, treatment approaches for ESCC in Eastern Africa have varied widely, with practice patterns determined by resource availability, as well as patients’ access and financial means. Many cancer referral centers in the region have been able to offer patients with advanced ESCC esophageal stenting with SEMS, radiotherapy with or without chemotherapy, or chemotherapy alone. Few centers host the infrastructure and trained personnel to consider patients for all three treatment modalities. However, access to different treatment modalities is beginning to improve as governments invest in expanding the oncology workforce, developing infrastructure for radiotherapy, and essential medicines for cancer care become more broadly available. Parallel to these efforts, access to SEMS for esophageal stenting has improved in recent years as a result of coordinated efforts within AfrECC to launch the Stent Access Initiative [14]. This program, launched in collaboration with Boston Scientific and the Clinton Health Access Initiative, established the first ever sustainable supply chain of high-quality and affordable SEMS for AfrECC sites in Kenya, Tanzania, Malawi, and Zambia. This access program has been paired with a Training-of-Trainer program focused on building endoscopic skills for SEMS placement without fluoroscopy [28]. As treatment options for ESCC become more widely available for patients across the region, the need to better understand the risks and benefits of the treatments in use and establish evidence-based practice guidelines becomes all that more pressing.

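### Complications are compared between treatment groups only by an unadjusted chi-squared test, so the safety comparison in this non-randomised cohort is open to confounding by patient condition and site

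*Protocol article*

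**What the plan says.** The Secondary endpoints section lists "major complications and treatment-related mortality" among the secondary endpoints, and the study objectives name safety as one of three treatment outcomes to be investigated. The only between-group analysis given for complications is in Statistical methods: "Complications will be summarized as number of patients (%) with 95% confidence intervals and compared between treatment arms by Chi-squared test". A later sentence in that section says that every analysis is run both overall and by site.

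Other endpoints are handled differently. Overall survival gets a Cox model with demographic and clinicopathological covariates. The dysphagia time-to-event outcomes are compared by "log-rank test and cph models to adjust covariates, including age, sex and baseline clinical covariates".

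On design, the article states: "This study is designed as a multi-center, prospective, observational, open cohort study". The Discussions section describes treatment of this cancer in the region as historically varied, "with practice patterns determined by resource availability" and by patients' access and financial means, and adds: "Few centers host the infrastructure and trained personnel to consider patients for all three treatment modalities".

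**The concern.** A chi-squared test on crude percentages estimates a treatment contrast only if the groups are otherwise comparable. Here a patient's treatment depends on the site reached, what that site offers, what the patient can afford and, plausibly, how ill the patient is. Site and illness can also affect the complication rate. The crude difference then mixes any effect of treatment with the effect of selection, and the test cannot separate them.

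This is more than a detail left for an analysis plan. The article names a specific test for a comparative safety endpoint and, in the next sentence, names covariate adjustment for the dysphagia outcomes. The study is meant to inform practice guidelines and the weighing of risks against benefits, so a confounded safety contrast could be read as a property of the treatment.

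**Working it through.** **The plan's own figures.** The article gives no rate, effect size or power for complications, so there is no safety figure to reproduce. Its only power figures are for overall survival. They do reproduce: for stenting against radiotherapy with or without chemotherapy, at a hazard ratio of 27/36 = 0.75 in the other direction of medians (36 against 27 weeks) and two-sided alpha of 0.0167, power is 0.993 with about 1209 events and 0.9998 if all 1778 patients die (stated: 0.99). They do not bear on complications.

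**Inputs from the Sample size section.** Stenting 1102. Radiotherapy with or without chemotherapy 464 + 212 = 676. All six groups: 1102 + 145 + 464 + 212 + 450 + 103 = 2476.

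**Assumptions (not in the document).** Complication risk is 10% in patients in good condition and 20% or 30% in those in poor condition, and is identical for both treatments within each level. Only the share of patients in poor condition differs between groups. The test is pairwise and two-sided.

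**Formulas.** Crude rate = (poor share × poor risk) + (good share × good risk). SE = √[p(1 − p)(1/1102 + 1/676)], with p the pooled rate. z = difference / SE. Chance of rejection at 0.05 ≈ P(Z > 1.96 − z), plus a small opposite tail.

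**One case in full.** Poor share 60% (stent) against 40% (radiotherapy), risks 10% and 30%.
- Stent: 0.6 × 30% + 0.4 × 10% = 22%. Radiotherapy: 0.4 × 30% + 0.6 × 10% = 18%.
- p = (1102 × 0.22 + 676 × 0.18)/1778 = 0.2048. SE = √(0.2048 × 0.7952 × 0.002387) = 0.0197.
- z = 0.04/0.0197 = 2.03. Chance of rejection ≈ 0.53, although treatment has no effect.

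**Range.** The last column is from 20,000 simulated studies per row, using a Mantel-Haenszel test stratified on condition. The same simulations agree with the crude column at 0.05.

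| Poor share, stent / RT | Risk, good / poor | Crude rates | Odds ratio | Crude test rejects at 0.05 | Crude test at 0.0167 | Stratified test at 0.05 |
|---|---|---|---|---|---|---|
| 50% / 40% | 10% / 20% | 15% / 14% | 1.08 | 0.09 | 0.04 | 0.05 |
| 60% / 40% | 10% / 20% | 16% / 14% | 1.17 | 0.20 | 0.10 | 0.05 |
| 60% / 40% | 10% / 30% | 22% / 18% | 1.28 | 0.53 | 0.36 | 0.05 |
| 70% / 30% | 10% / 30% | 24% / 16% | 1.66 | 0.98 | 0.95 | 0.05 |

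With equal shares (50% / 50%, risks 10% and 30%) the crude test also rejects about 5% of the time.

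**Direction.** Swap the shares in the third row (40% stent, 60% radiotherapy). The crude rates become 18% and 22%, z = 0.04/0.0194 = 2.07, and the chance of rejection is about 0.54, now against radiotherapy. Nothing in the article settles which way the imbalance runs.

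**Does the within-site repeat help?** In Table 1, stents and on-site external beam radiotherapy are both available only at Moi Teaching and Referral Hospital, with 320 of 2476 forecast patients (12.9%). Kamuzu Central lists radiotherapy as planned, Kilimanjaro refers to Ocean Road, Tenwek and Muhimbili have none, and Ocean Road has no stents. Referral may create some further overlap, but most of the stent-radiotherapy contrast lies between sites. Within a site, patient condition is still unadjusted.

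**The case against.** The other side has real points.

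- **Partial controls exist.** The within-site repeat deals with site differences where a site offers both modalities, and the plan will tabulate patient characteristics by modality, so imbalance will be visible. Seeing an imbalance does not correct the comparison.
- **Multiplicity.** The plan applies a Bonferroni correction. At 0.0167 the crude test rejects less often (0.04 to 0.95 in the table), but still well above its nominal level. Bonferroni does not remove bias.
- **The rates are assumed.** This stands. The range shows the mechanism and does not predict the result.

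A reader might also infer more than the article supports:

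- **That benefit is adjusted and harm is not.** Quality of life is a benefit outcome, and its tests and GEE model also name no covariates. The line runs between the Cox-modelled endpoints and the rest.
- **That treatment- and disease-related events are pooled.** Chart abstraction lists "major treatment- and disease-related complications" and Table 3 has one row for complications. A list and a summary row do not show how the case report form records attribution, and the form is not shown.
- **That sicker patients get stents, making a false signal against stenting likely.** The remark that "SEMS may be advantageous for those with short life expectancies" is the rationale for a prognostic index developed elsewhere, which the article says predicted poorly in a South African population. The survival medians in the Sample size section (36 weeks for stenting, 27 for radiotherapy with or without chemotherapy) give that inference no support.

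**Conclusion.** The point holds as a limited one. The article fixes an unadjusted test as the only between-group analysis of a named secondary safety endpoint in a non-randomised cohort, and the within-site repeat does not replace adjustment. The comparison is open to confounding by patient condition and site.

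The size and direction of the bias cannot be derived from the document. Under the assumed imbalances with no true effect, the crude test at 0.05 rejects about 9% to 98% of the time, against about 5% for a stratified test. This rests on the forecast group sizes, assumed risks of 10% and 20% to 30%, and a confounder that is measured and fully adjusted for. With no imbalance there is no problem. No single value in that range should be quoted as the expected error rate. The change is worth making because the main adjustment variables are already collected. The primary survival analysis is not affected.

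**What to change.** In Statistical methods, keep the number and percentage of patients with 95% confidence intervals as description. Make the between-group comparison a logistic or modified Poisson regression of major complications on treatment, adjusted for age, sex, baseline WHO performance status and baseline dysphagia score. Tables 2 and 3 show that all four are collected at baseline.

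- **Site.** Add it as a covariate or stratum where modalities overlap. State plainly that stent-radiotherapy overlap within sites is limited, so part of that contrast cannot be separated from site.
- **Tumour length and location.** Use these only in a sensitivity analysis. Table 3 lists them as endoscopic findings, diagnosis by barium swallow alone is allowed, and Ocean Road, a radiotherapy site, has no endoscopy. They are likely to be missing for some patients, possibly unevenly by treatment.
- **Attribution.** Where it is recorded, report treatment-related and disease-related complications separately. Patients on supportive care alone have no directly comparable treatment-related outcome.

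The cost is a short change to the analysis text, with no new data for the main model. Intervals will be wider than the crude ones, and if events are rare the model must carry fewer covariates.

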#### Patient interviews

Interviews with study participants will be conducted at the following specified time-points: (i) at time of study enrollment); (ii) prior to the initiation of treatment (within 4 weeks); and (iii) during post-treatment follow up (1 month after initiation of treatment, 3 months after initiation of treatment, and then every 3 months until death or loss to follow up). Research assistants will collect data on sociodemographic characteristics, medical history, and baseline QOL through face-to-face administration of oral questionnaires at the time of study enrollment. QOL assessments are based on the ‘Modified Rosenblatt Index,’ [16] a questionnaire comprised of six patient-reported outcomes assessing for the presence and severity of the following as scored on a Likert scale: Odynophagia, Dysphagia, ‘Chest and/or Back pain,’ WHO performance status, and ‘Overall Well-being’ since starting treatment (see Table 2). Subsequent interviews assessing vital status and QOL will be performed through mobile phone outreach. During post-treatment follow up, research assistants will attempt to contact patients a minimum of three times over the follow up interval before patients are classified as “lost to follow up.” Outreach attempts will be made at varying times of the day on three different days of the week.

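### Log-rank and Cox are not valid for dysphagia-adjusted survival under censoring, and time to relief needs methods for call-dated events and for death

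*Protocol article*

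**What the plan says.** The Secondary endpoints section lists four dysphagia outcomes: "time to achieve any dysphagia relief, time to achieve maximal dysphagia relief, duration of dysphagia relief, and dysphagia-adjusted survival". The Statistical methods section gives them one shared analysis among the palliative treatments: "secondary outcome measures related to dysphagia will be compared using log-rank test and cph models to adjust covariates".

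Time to any relief is "time from treatment to improvement in dysphagia score of greater than or equal to 1". Dysphagia-adjusted survival "will be defined as the total time period with a dysphagia score of 0 to 2".

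After the pre-treatment score, the Patient interviews section schedules assessments "1 month after initiation of treatment, 3 months after initiation of treatment, and then every 3 months until death or loss to follow up". Table 3 marks no quality-of-life assessment during treatment. The Study design section gives follow-up of at least 6 and at most 53 months.

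The article does not say how death before relief is handled. For these outcomes it names no method for interval censoring, for competing events or for censored quality-adjusted time.

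**The concern.** Dysphagia-adjusted survival is accumulated good time, not elapsed time. Suppose two patients are both lost at week 20, one with 95% good time and one with 20%. They are censored at 0.95 × 20 = 19 weeks and 0.20 × 20 = 4 weeks. The censoring value therefore carries information about the outcome, although the loss itself was random. Log-rank and Cox assume that it does not. If relief comes early under one treatment and late under another, the bias differs between groups and can create a treatment difference where there is none.

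Time to relief raises two lesser issues. Relief on day 3 and relief on day 25 are both first seen at the 1-month call, yet log-rank and Cox take the call date as exact. And with relief as the only event, both methods by default censor patients who die unrelieved, as though they could still improve. Death rates before the calls differ widely between treatments, so a probability of relief read from such an analysis would be inflated unequally.

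**Working it through.** **Figures in the plan.** No power or sample size is attached to any dysphagia outcome. The stated overall-survival power does reproduce. For stenting vs radiotherapy, HR = 27/36 = 0.75, with 1102 and 464 + 212 = 676 patients and two-sided alpha 0.0167. The Schoenfeld formula gives 0.993 (1210 events) to 0.9998 (all 1778 die), against 0.99 stated. Median survivals of 36, 27 and 14 weeks (stent, radiotherapy, chemotherapy) are used below with exponential survival, which is an assumption.

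**1. Dysphagia-adjusted survival: bias in one group.** Assumptions: median survival 30 weeks; half the patients have 20% good time and half 95%; administrative censoring uniform from 26 to 204 weeks; random loss on top.
- True median q solves 0.5·2^(−q/6) + 0.5·2^(−q/28.5) = 0.5, where 6 = 0.20 × 30 and 28.5 = 0.95 × 30. At q = 11.94 the terms are 0.252 and 0.748, which average 0.50.
- Simulated Kaplan-Meier medians (n = 200,000):

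| Total censored | KM median (weeks) | Ratio to 11.94 |
|---|---|---|
| 13% (end of study only) | 12.2 | 1.02 |
| 35% | 13.6 | 1.14 |
| 49% | 15.3 | 1.28 |

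**2. Dysphagia-adjusted survival: bias in the comparison.** Assumptions: 1102 vs 676 patients, median survival 30 weeks in both groups, the same true distribution of good time (share drawn from Beta(3,2)), and administrative censoring from 26 to 176 weeks. Good time starts at once in one group and up to 6 weeks late in the other. There were 300 runs at nominal 0.05, so the Monte Carlo error is √(0.05 × 0.95/300) = 1.3 points.

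| Assumed loss | Log-rank rejects | Spurious HR | KM medians, early vs late relief (true 16.6) |
|---|---|---|---|
| 0% | 6% | 0.98 | 16.9 vs 16.8 |
| 10% | 7% | 0.97 | 17.3 vs 17.0 |
| 20% | 12% | 0.955 | 17.9 vs 17.2 |
| 30% | 13% | 0.94 | 18.5 vs 17.5 |

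A separate run with the same 6-week delay rose from 5% to 18% as loss grew. With identical timing in both groups and 20% loss, rejection was 4%. If all good time falls last in one group, an extreme case, rejection was 78% to nearly 100%. The error favours the treatment whose relief comes first.

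**3. Deaths before the calls.** The probability is 1 − 2^(−t/median), with 1 month = 4.35 weeks and 3 months = 13 weeks.

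| | Stent | Radiotherapy | Chemotherapy |
|---|---|---|---|
| Before 1 month | 8.0% | 10.6% | 19.4% |
| Before 3 months | 22.1% | 28.4% | 47.5% |

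**4. Probability of relief at 26 weeks.** Let h be the relief hazard and d the death hazard. With deaths censored, 1 − KM = 1 − exp(−26h). With death competing, cumulative incidence = h/(h+d) × [1 − exp(−26(h+d))]. Assume the same median time to relief of 8 weeks in every group, so h = ln2/8 = 0.0866.
- 1 − KM = 0.895 in all three groups.
- Stent: d = ln2/36 = 0.0193; 0.818 × (1 − 0.064) = 0.77.
- Radiotherapy: d = ln2/27; 0.73.
- Chemotherapy: d = ln2/14 = 0.0495; 0.636 × (1 − 0.029) = 0.62.

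With an assumed median of 13 weeks, 1 − KM is 0.75 and the cumulative incidences are 0.62, 0.59 and 0.48.

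**The case against.** Much can be said for the plan.

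- **Early versus late relief.** A reader might infer that a first look at 1 month prevents the study from telling early from late relief. It does not. Take exponential relief times with medians of about 2 days and 3 weeks. By the 1-month call more than 99.9% and 63% (1 − 2^(−4.345/3)) have been relieved. Log-rank on the call dates rejected in 300 of 300 simulated runs, and did so even with 100 vs 60 patients. Only timing among patients who are all relieved before that call is lost. The plan also compares scores at each visit and by GEE.
- **Purpose.** A reader might take these outcomes to be built to test rapid against delayed relief. The Discussions section does say "SEMS have been shown to provide immediate dysphagia relief" and that radiation acts later, but as background. Neither the objectives nor the endpoint text makes it their hypothesis.
- **Death.** A reader might take it that the plan states that deaths are censored. It is silent. Censoring is only the default of log-rank and Cox for time to relief, where it gives a legitimate comparison of cause-specific relief hazards. For dysphagia-adjusted survival, death is the end event.
- **Size.** Kaplan-Meier is named for overall survival, not for these outcomes, so the inflated probabilities arise only if such curves are reported. For a stent with a 2-day median the gap is under one point (99.2% vs 100%). The larger bias figures rest on assumed loss rates and good-time splits.

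All of this stands and limits the point. None of it rescues log-rank and Cox on accumulated good time: that method is stated, and it is not valid once there is censoring, which staggered entry makes certain.

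**Conclusion.** The firm part is dysphagia-adjusted survival: the article fixes an analysis whose censoring assumption fails by construction. With end-of-study censoring only the effect is small, about 2% in a Kaplan-Meier median and a type I error near 5-6%, which is hardly distinguishable from nominal. It grows with loss and with differences in relief timing: about 14-28% in a median at an assumed 35-49% total censoring, and a type I error of roughly 6-18% with an assumed 6-week delay. The article gives no loss rate, so the upper figures are conditional.

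For time to relief the point is narrower. Differences within the first month among patients all relieved by the first call cannot be seen, and call dates are interval-censored. With about 8%, 11% and 19% dying before that call, a reported probability of relief that censors deaths would be too high, most in the shortest-lived group. These are secondary outcomes with no stated power. The analysis should be changed, but the primary comparison is untouched.

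**What to change.** **Dysphagia-adjusted survival.** Replace log-rank and Cox with restricted mean time alive with score 0-2 over a fixed window from treatment start, for example 26 weeks. Compare treatments by covariate-adjusted regression, with inverse-probability-of-censoring weights for patients lost or administratively censored within the window. The weights are needed because the 6-month minimum does not guarantee 26 weeks after treatment when treatment starts late, and because loss also occurs inside the window.

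**Time to relief.** Report cumulative incidence of relief with death as a competing event, alongside the Cox model, which should be labelled cause-specific. Treat call-dated relief as interval-censored.

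**Cost.** A little more analysis work, no new data, and good time beyond the window is not counted. A recall question at the 1-month call on when swallowing improved would add little: recruitment began in February 2019, so it would miss patients already called and those who die before the call.
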